#### Concealment mechanism

Allocation will be performed at the clinic level, not the participant level. To minimize the possibility of selection bias at the cluster level, the health care clinics will be identified and recruited prior to randomization. Cluster allocation will be concealed from administrative staff of the primary care clinics who could come into contact with the recruiters. Likewise, cluster allocation will be concealed from the recruiters [41].

#### Implementation

A member of the research team who is not involved in the recruitment process in primary care clinics will be in charge of the generation of the random sequence and the allocation of the clusters to the interventions. Cluster allocation will be kept concealed from the recruiters; to do this, the process will be hidden from administrative staff of the primary care clinics who could come into contact with the recruiters, who will be expressly instructed not to contact health care personnel at the participating centers.

### Assignment of interventions: blinding

#### Who will be blinded

Due to the nature of the interventions, it will not be possible to blind the providers or the patients who participate in the trial. Outcome assessments will be conducted by an evaluator blinded to the allocation of the interventions. These evaluators will be trained to administer the battery of evaluation instruments, but will not be given any details about the procedures involved in the study.

#### Procedure for unblinding if needed

Not applicable.

### Data collection and management

#### Plans for assessment and collection of outcomes

Technical staff in charge of the assessments and data collection will be selected considering their prior experience in survey administration. In addition, they will participate in a training session focused on the administration of the battery of instruments of the trial and will receive permanent supervision from the person in charge of recruitment and/or research team members. Specifically, baseline evaluations will be conducted by the recruiters, while follow-up evaluations (3, 6, and 12 months) will be carried out by the outcome evaluators. The baseline and outcomes assessments will be conducted in-person – or remotely, if this is not possible (e.g., telephone calls).

The outcomes section lists the measurement instruments for each follow-up assessment: PHQ-9, SF-12, SPSI-R:S, an ad-hoc instrument for assessing the acceptability of depression treatment, and a questionnaire about the utilization of health care services and treatment adherence. These instruments will be described below. Blood pressure and glycosylated hemoglobin data will be retrospectively collected from the clinical records of each participant by outcome evaluators blinded to the allocation of primary care clinics.

The PHQ-9 is one of the world’s most widely used measures for self-reporting depressive symptoms. It has been validated for use with primary care populations, which will make it possible to study major depression as an estimate of the intensity of depressive symptoms (i.e. severity of the condition) [36]. The PHQ-9 comprises nine questions based on the diagnostic criteria for depressive episodes described in the Diagnostic and Statistical Manual of Mental Disorders, fourth edition (DSM-IV); each of these questions has four answer choices, which make it possible to evaluate the intensity of each symptom [36]. The scale ranges from 0 to 27 points, with the following gravity classification: no depression (0 to 4 points), mild depression (5 to 9 points), moderate depression (10 to 14 points), moderate-severe depression (15 to 19 points), and severe depression (20 or more points). In the original validation study for its use in primary care, a cutoff score of 10 points or more had a sensitivity and specificity of 88% for major depression [36]. The PHQ-9 has been validated for use with primary care populations in Chile [42].

Nowadays, the multiple versions of SF questionnaires (i.e. 8, 12, and 36) are the reference standard for assessing health and well-being from the patient’s perspective, having been validated for use with a variety of populations worldwide. Specifically, the SF-12 –a reduced 12-item version of the SF-36– is easier to understand and administer and is less taxing for patients than the original version [37]. The SF-12 comprises eight scales (physical functioning, role-physical, bodily pain, general health, vitality, role-emotional, social functioning, and mental health) and two principal components (physical component summary and mental component summary), with items that have a 4-week recall period and scores ranging from 0 (worst health possible) to 100 (best health possible) [37]. The SF-12 has been validated for use with beneficiaries of public and private health care in Chile [43].

The SPSI-R:S is a self-report instrument that assesses individual social problem resolution skills based on the five-component Model of Social Problem-Solving developed by D’Zurilla and Nezu [38]. This questionnaire has been widely used around the world, is easy to administer, and has good psychometric properties. The SPSI-R:S comprises 25 Likert-type items with five answer choices ranging from 0 (not at all true) to 4 (extremely true), and has five subscales: Positive Problem Orientation, Negative Problem Orientation, Rational Problem Solving Style, Impulsivity/Carelessness Style, and Avoidance Style [38].

The ad-hoc instrument for evaluating the acceptability of the interventions is a self-report questionnaire that consists in 12 Likert-type items with four answer choices ranging from 1 (strongly agree) to 4 (strongly disagree). The construction of this instrument was based on the theoretical framework of acceptability, proposed by Sekhon et al. [44], which characterizes seven dimensions for this concept: ethicality, affective attitude, burden, opportunity costs, perceived effectiveness, self-efficacy, and intervention coherence. For their interpretation, the participants’ scores were transformed into percentages (0 to 100%), with higher values representing more intervention acceptability.

The questionnaire about the utilization of health care services, adapted from the National Socioeconomic Characterization Survey [45], has a 3-month recall period and records physician consultations or treatments, primary care and/or hospital emergencies, specialist medical treatment or mental health treatment, and hospitalizations, noting the total number of sessions (total days for hospitalizations) and the payment made for each session. In addition, two self-report questionnaires will be administered to evaluate treatment adherence: and ad-hoc questionnaire and the Batalla Test [46]. The ad-hoc questionnaire will comprise a series of dichotomous questions about medication adherence. The Batalla Test, on the other hand, evaluates the patient’s knowledge about his/her disease with three questions, assuming that more patient knowledge reflects more adherence.

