A computer-assisted, psycho-educational intervention, delivered in-person –or remotely if this is not possible– by trained therapists participating in the trial, at the selected primary care clinics. Eight individual sessions will be held in total, each lasting 45 min. Sessions will be held weekly at first (4 sessions), followed by 4 monthly sessions. The intervention manual will ensure standardized implementation of each session. The manual carefully details the aims, activities, necessary materials, and possible conversations with the patient in each session. The therapists participating in the trial will deliver this intervention with the support of a laptop computer to display slides or videos. This intervention will combine education about health issues (depression, diabetes, and hypertension), basic elements of motivational interviewing, and cognitive-behavioral techniques to involve the patients in the management of their own health issues, encourage behavioral activation, improve problem-solving skills, and modify negative thoughts. The first two sessions, based on health education and motivational interviewing, will actively involve the patients in managing their health issues and will establish a link between depression and chronic diseases, specifying their impact on the patients’ quality of life. Also, a personalized care plan will be developed. The patients will receive support materials such as calendars and a blackboard-type care plan. Sessions three and four will address negative thoughts and problem-solving techniques. The fifth session will incorporate elements of behavioral activation, while the sixth will pay closer attention to thinking errors. In all sessions, the patients’ progress in their care plan will be reviewed. The last two sessions (reinforcement sessions) will elaborate on the associations between the topics covered in each session and will feature the closing activities. The therapists will record information about the topics covered in the sessions in the electronic health records of the participating primary care clinics. The therapists will all be psychologists. Their training will consist in a 12-h induction about the basics of the intervention. This training program will include teaching sessions, role playing, and knowledge tests, which will be in charge of the research team. The therapists will participate in a biweekly supervision by a psychologist from the research team to solve logistical problems and issues with treatment integrity.Telephone monitoring will be in charge of a social worker participating in the trial. Monitoring calls lasting 5 to 10 min will be made during the first 12 weeks of the intervention, once per week, in order to observe the patients’ clinical evolution, the medical care received, and their use of antidepressants and possible collateral effects, while also encouraging adherence to the medical and psycho-educational treatment. The social worker in charge of telephone monitoring, who has a long experience in managing cases in clinical trials for depression treatment, will have a standardized form for recording information.A psychiatrist from the research team will review the social worker’s caseload to formulate treatment recommendations and solve health care problems affecting the patients throughout the study. In addition, the psychiatrist will monthly supervise the study therapists to assist them in the management of the most severe cases and in the collaboration with routine primary care.Once per month, a member of the research team will meet with the teams from the participating primary care clinics. These meetings will be aimed at integrating the mental health care provided by the study therapists with the usual medical care for chronic diseases provided in the cardiovascular health program of each primary care clinic, to ensure continuity of care.Usual medical care for chronic diseases, according to the Cardiovascular Health Program.

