#### Strategies to improve adherence to interventions

Adherence to trial protocols will be ensured by training and supervising the therapists taking part in the trial. In addition, the therapists and the social worker will be asked to keep a record of each session with the patients, which will be reviewed by a psychiatrist from the research team to ensure adherence to the protocols. Lastly, 10% of the participants will be contacted by a blinded evaluator who will administer an ad-hoc questionnaire designed to assess the therapists’ fidelity to the intervention.

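### Evaluator blinding is put at risk, with no stated protection, because the PHQ-9 evaluators also collect blood pressure and HbA1c from clinical records that probably hold trial session notes

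*Protocol article*

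**What the plan says.** All references are to the protocol article.

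- *Who will be blinded*: patients and providers cannot be blinded. "Outcome assessments will be conducted by an evaluator blinded to the allocation of the interventions". These evaluators are trained on the instruments "but will not be given any details about the procedures involved in the study".
- *Plans for assessment and collection of outcomes*: the "follow-up evaluations (3, 6, and 12 months) will be carried out by the outcome evaluators", and the PHQ-9 is among the instruments used at each of them. The same section adds that blood pressure and HbA1c values are "retrospectively collected from the clinical records of each participant by outcome evaluators blinded to the allocation of primary care clinics".
- *Active arm*: "The therapists will record information about the topics covered in the sessions in the electronic health records of the participating primary care clinics". The therapists are trial staff, and their sessions are given only in intervention clinics.
- *Concealment mechanism*: the unit of allocation is the clinic.
- *Strategies to improve adherence to interventions*: "10% of the participants will be contacted by a blinded evaluator who will administer an ad-hoc questionnaire designed to assess" the therapists' fidelity.

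**The concern.** Three statements do not sit well together: the evaluators are blind to clinic allocation, the evaluators collect data from clinical records, and trial therapists document the intervention in clinic records. An evaluator who looks up a blood pressure value could come across notes of a structured programme that exists in one arm only. In a cluster trial, that discloses the arm of the whole clinic and not just of one patient.

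The Abstract calls the trial single-blind. Since patients and providers know the treatment, evaluator blinding is the only blinding left during follow-up. The primary outcome is collected by these evaluators, possibly by telephone, and entered by them in electronic forms. It is then cut at a 50% reduction from baseline. With a baseline PHQ-9 of 16, for example, a follow-up score of 8 is a response and a score of 9 is not, so a small difference in how an item is put or probed can change the classification.

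**Working it through.** **Numbers.** The cluster size reproduces: 38 / (1 − 0.15) = 44.7, rounded up to 45, and 45 × 8 = 360. One clinic is 45 / 360 = 12.5% of the sample. The four intervention clinics are 4 × 45 = 180, or 50%. After the planned attrition the share of one clinic is the same: 38 / (8 × 38) = 38 / 304 = 12.5%. These are counts of participants whose arm could become known; they do not estimate bias.

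**Are the records the same?** *Active arm* speaks of electronic health records of the clinics, and *Plans for assessment and collection of outcomes* speaks of clinical records of participants. Blood pressure and HbA1c come from usual care in each clinic's Cardiovascular Health Program, so one shared record is the natural reading. It remains an inference.

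**Would notes be there in time?** The schedule is four weekly sessions followed by four monthly ones, about five months in all. If sessions start soon after enrolment (an assumption), several notes exist by month 3 and the full set by month 6, when the primary outcome is taken.

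**Does the timing of extraction protect the PHQ-9?** The article says only that the collection is retrospective. Three readings are possible:

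1. *Extraction at each wave.* The secondary outcome is reported at 3, 6 and 12 months, so this is plausible. An evaluator who opens records after the 3-month visit could know the arm before the 6- and 12-month PHQ-9 interviews.
2. *Extraction after each participant's own last interview.* That participant's PHQ-9 is safe. Later-enrolled participants at the same clinic may still be due for interview, and clinic-level allocation carries the knowledge over to them.
3. *Extraction after the last 12-month interview in all clinics.* No PHQ-9 interview can be affected.

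Only the third reading closes the route by timing alone, and the text does not require it. Nor does it mention a separate extractor or an export limited to values.

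**Comparison with recruitment.** For recruiters, *Implementation* describes steps that keep allocation hidden, including an instruction about contact with clinic personnel. No comparable step is given for evaluators, although they are sent to the clinics' records.

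**Which outcome is exposed?** Blood pressure and HbA1c are values already recorded by clinic staff. Knowledge of the arm leaves the extractor little room beyond choosing which reading counts for a visit. The main concern is therefore carry-over to the PHQ-9.

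**Fidelity questionnaire.** It asks how therapists kept to the intervention, and trial therapists deliver sessions only in intervention clinics. A person who asks these questions and hears the answers can hardly remain blind to the arm of those respondents. The article does not say whether this person also assesses outcomes.

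**The case against.** A reader might infer that the plan itself breaks the blinding. The text does not go that far, and several counter-arguments have force.

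- The identity of the two record systems is not stated, and extraction could be confined to vital-sign and laboratory fields. This stands.
- Retrospective collection may mean collection after all interviews, in which case the PHQ-9 is untouched. This stands as a possibility, but the wording fits the other two readings equally well.
- Evaluators are told nothing about the study procedures, so they may not recognise a trial note. This reduces the risk. It does not remove it, since notes of a manualised programme that recur in some clinics and are absent from others can be noticed without a briefing.
- Guideline care in the control arm includes psychotherapy for severe cases, so notes of psychological care can occur in both arms. This stands. A reader might infer that any single opened record unblinds a clinic, but only a recognised trial note could do so, and a control record could reveal its arm only through absence, which one record cannot establish.
- The PHQ-9 is a self-report scale with fixed answer choices and is not an evaluator's rating. This limits the scope for influence, although the evaluator still administers it and enters the data.
- An article may leave extraction details to the full protocol. This is partly fair. Here, however, the article itself names the source, the collector and the blinding claim, and the three need to be reconciled.

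A reader might also infer a bias of several percentage points against the 23 planned. Nothing in the document supports such a figure. If a share *f* of an arm lies near the threshold and a share *r* of those is reclassified, the arm's response rate moves by *f* × *r*. With assumed values of *f* from 10 to 30% and *r* from 3 to 5%, that is 0.10 × 0.03 = 0.3 points to 0.30 × 0.05 = 1.5 points, and movements in the same direction in both arms largely cancel. Neither input comes from the article.

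**Conclusion.** The point holds as a risk without a stated protection. Evaluators who are described as blind, and who conduct the PHQ-9 interviews, are sent to records that most naturally contain arm-identifying notes. If a trial note is recognised, the arm of about 45 participants (12.5% of the sample) at that intervention clinic could become known before later PHQ-9 interviews. This rests on three assumptions: the clinical and the electronic records are the same, the evaluators can see session notes, and extraction takes place while interviews are still running. The article neither confirms nor excludes any of them. The size of any bias in the response difference cannot be derived from the document.

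The wording on the fidelity evaluator is a smaller, separate inconsistency. A reader might take it as further evidence that the primary outcome is unblinded, but the article does not identify that person as an outcome evaluator.

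Severity: should-fix, with moderate confidence.

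**What to change.** In *Plans for assessment and collection of outcomes*, state one of the following:

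- blood pressure and HbA1c are extracted only after the last 12-month PHQ-9 interview in all clinics; or
- they are supplied to the evaluators as a structured export of dates and values, without clinical notes.

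Either change leaves the therapists' documentation as it is. The first costs only the later availability of these secondary outcomes, since no interim analysis is planned. The second needs an export to be arranged with the clinics.

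In *Strategies to improve adherence to interventions*, remove or explain the word blinded for the person who asks about fidelity, and state that this person does no outcome assessments. This is an allocation of tasks among staff.

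Two steps are optional good practice and do not correct an error: administering the PHQ-9 before the acceptability and service-use questionnaires, whose answers may reveal the treatment, and having evaluators record their guess of the allocation.

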#### Intervention description

Patients in the primary care clinics assigned to the intervention and to the comparator will have access to the project’s website, which will be populated with information about the project’s aims, the research team, and contact data, along with educational material related to depression, diabetes and hypertension, and healthy lifestyles.

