
#### Control arm

The patients in the primary care clinics assigned to the comparator will receive the usual treatment for depression and their physical conditions –all the guaranteed interventions for people with depression, hypertension, and/or diabetes in primary care, according to the Clinical Guidelines for the Treatment of Depression– and their associated basket of health benefits included in the Regime of Explicit Health Care Guarantees [34, 35].

In the specific case of depression, in Chile, this pathology is managed using a stepped care model, with more severe cases being addressed with more intense and frequent interventions [34]. The severity of depression is determined with the diagnostic criteria of the International Classification of Diseases, tenth version (ICD-10), which characterizes mild, moderate, and severe levels depending on the number of symptoms [34]. Mild cases are treated with low-intensity interventions such as counseling, support groups, and physical exercise programs; moderate cases are complementarily treated with antidepressants, depending on patients’ response and tolerance; finally, the treatment of severe cases also includes psychotherapy [34]. Depression cases with high suicide risk or psychotic symptoms, or which are refractory to treatment, are referred to psychiatric assessment or to specialized mental health services [34].

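### The Batalla Test scores disease knowledge, which the trial teaches in sessions to the active arm only, so a between-arm difference on it could reflect teaching rather than treatment adherence

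*Protocol article*

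**What the plan says.** Under Plans for assessment and collection of outcomes, the article states that "two self-report questionnaires will be administered to evaluate treatment adherence". The first is described thus: "The ad-hoc questionnaire will comprise a series of dichotomous questions about medication adherence". The second, the Batalla Test, "evaluates the patient’s knowledge about his/her disease with three questions", and is interpreted by "assuming that more patient knowledge reflects more adherence".

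Under Active arm, the content of the eight individual sessions is introduced with "This intervention will combine education about health issues (depression, diabetes, and hypertension" and goes on to motivational interviewing and cognitive-behavioural techniques. The education is placed at the start: "The first two sessions, based on health education and motivational interviewing".

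Under Control arm: "The patients in the primary care clinics assigned to the comparator will receive the usual treatment for depression and their physical conditions". Under Intervention description: "Patients in the primary care clinics assigned to the intervention and to the comparator will have access to the project’s website". The site carries educational material on the same diseases.

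The section Other measures lists treatment adherence, with health service use, for evaluation at 3, 6 and 12 months. Adherence does not appear among the primary or secondary outcomes.

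**The concern.** A knowledge test can stand in for adherence in a comparison of arms only if the arms have no separate route to a higher score. In this trial one arm has such a route, because its sessions teach about the diseases that the test concerns. Knowledge and adherence may go together among patients who have not been taught. That does not mean that knowledge added by teaching brings a matching change in adherence.

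What is at stake is the meaning of one result. If the active arm scores higher, the article's interpretive rule leads to a statement that adherence improved, although the score alone cannot separate that from the education having been absorbed. The Discussion cites increased adherence to diabetes and/or hypertension treatment among the promising pilot findings, so such a statement would be of interest to readers. The article does not say which instrument the pilot used.

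**Working it through.** No arithmetic applies. The article gives no figure for this test, so there is none to reproduce. The check sets the sections side by side.

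1. **What is scored.** Disease knowledge, by three questions (Plans for assessment and collection of outcomes).
2. **What it is taken to mean.** Treatment adherence, by a declared assumption (same section). This is a stated rule of interpretation, not a detail left for a fuller document.
3. **What the active arm receives.** Individual therapist-led sessions that include education on depression, diabetes and hypertension, concentrated in the first two of eight (Active arm). The first four sessions are weekly. If they begin soon after enrolment, the teaching is complete before the first follow-up at 3 months, and so before every planned assessment.
4. **What the control arm receives.** Usual treatment for depression and for the physical conditions, without the trial's sessions (Control arm). All participants are already enrolled in the Cardiovascular Health Program (Trial participants), so some disease education in usual care is possible. The article neither describes nor excludes it.
5. **What both arms share.** The website (Intervention description). It may narrow a knowledge gap, but being common to both arms it does not remove the additional teaching in one of them.
6. **Consequence.** A between-arm difference in the score can have two sources: knowledge that goes with a change in adherence, and knowledge added by the sessions without one. The test records only the total. The intervention may also truly raise adherence, since its weekly calls over 12 weeks encourage it, but the Batalla score cannot show which source is at work.
7. **Direction.** Added teaching should raise knowledge if it changes it at all, so the expected distortion favours the intervention.
8. **Reach.** The second instrument asks about medication adherence directly, so the problem is confined to the Batalla score and to any reading that combines the two.

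**The case against.** The case on the other side has several parts.

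- **The knowledge contrast is assumed, not shown.** Controls receive all guaranteed care for depression, hypertension and diabetes, and all participants are already under treatment in the cardiovascular programme. A reader might infer that their only source of education is the website; the article does not support that. This stands, and it limits how firmly a gap can be predicted.
- **The items are not visible.** If they ask for basic facts that treated patients already know, the sessions might not move the score. This also stands. It is a reason to say that teaching could produce a difference, not that it would.
- **A size cannot be given.** One might reason that one more correct answer out of three shifts a patient by a third of the scale. That presumes equally weighted items and a summed score, and the article gives no scoring rule.
- **No adherence claim is planned.** Adherence is absent from the specific objectives, the hypotheses and the primary and secondary outcomes, and the article does not say which instrument would carry a claim. This is right as to importance. The rule that knowledge stands for adherence is nonetheless written down, and the two instruments are not ranked, so a favourable Batalla result could be reported as an adherence benefit.
- **The assumption is disclosed.** It is, and openly. Disclosure does not make it hold equally in both arms when one arm is taught.
- **The remaining questionnaire is not free of bias.** It is ad hoc self-report, the section Who will be blinded says that patients cannot be blinded, and only the active arm receives calls that encourage adherence. This stands in full and belongs with the fix as a cost.

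**Conclusion.** The concern holds in a limited form. As described, the Batalla Test cannot by itself support a between-arm statement about treatment adherence, because a difference could come wholly or partly from the active arm's education sessions. The expected direction favours the intervention, and the size cannot be estimated from the article.

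This rests on two assumptions: that the three questions overlap at least in part with what the sessions teach, and that usual care and the website do not fully close the gap. Both are plausible from the article's description, but neither is demonstrated.

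A reader might go further and infer that the trial's evidence of effectiveness is biased. The article does not support that. Adherence is an additional measure, and neither the PHQ-9 response at 6 months nor any secondary outcome depends on this test. The point is a low-cost improvement.

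**What to change.** Keep administering the Batalla Test at 3, 6 and 12 months, but report it as disease knowledge, a process measure of whether the education component was taken up. Base between-arm statements about adherence on the medication-adherence questionnaire already in the battery, and do not combine the two scores into one adherence result.

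No new data, visits or participants are needed: one measure is relabelled and a sentence is added to the analysis plan. The cost is that adherence then rests on a single ad-hoc self-report questionnaire, for which the article reports no validation, completed by unblinded patients of whom only the active arm is called weekly and encouraged to adhere. Differential self-report is possible there too, so this limitation should be stated beside the adherence result.
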